### Sample Size Estimation

Considering the average values of pressure/saturation/HR among a general population with a sample of 3000 participants, there will be a power exceeding 95% for all evaluated parameters in a 2-sided test with a *P* value of .05 if the discrepancy between the 2 measurement methods is as reported in Table 2.

**Table 2 table2:** Expected error level of the measurements.

Vital	Range	Unit of measurement	Error level
Pulse rate	50-180	BPM^a^	RMSE^b^ ≤3
Respiratory rate	8-30	BrPM^c^	RMSE ≤3
Blood pressure systolic	80-180	mm Hg	MAE^d^ ≤15
Blood pressure diastolic	50-120	mm Hg	MAE ≤10

^a^BPM: beats per minute.

^b^RMSE: root mean square error.

^c^BrPM: breaths per minute.

^d^MAE: mean absolute error.

### Known Potential Risks and Benefits of the Investigational Device

#### Potential Risks

No adverse device effects are expected from the Comestai app, and there are no contraindications for its use in the study population. However, unforeseeable risks related to the data collection process may arise.

One such risk is the potential breach of participant confidentiality due to improper data storage. In order to mitigate this, vital signs data will be securely stored on Comestai’s cloud. Videos of faces obtained using the “by face” method will be anonymized, and recognized only by the participant identification number assigned during screening. The raw vital signs data will be locked, encrypted, and accessible solely by the study center team. Processing of this data will only occur once the files are unlocked.

#### Potential Benefits

Participants in this study will not receive direct benefits. However, the data gathered may aid in the advancement of the Comestai noninvasive software app for monitoring vital signs. Progress in this area has the potential to enhance patient care quality and reduce labor time and costs within the health care system.

Advances in this field may improve the quality of care provided to patients and save labor time and costs for the health care system.

### Ethics Approval

The study was approved by the ethics committee (Comitato Etico Territoriale Lombardia 1, Milano, Italy, approval code CET 98-2024). The study will be conducted according to the Declaration of Helsinki guidelines, international guidelines, and current clinical trial laws.

All participants will give their written consent after being fully informed about the study. For individuals younger than 18 years, both legal guardians’ written consent and assent by adolescents themselves will be collected.

Data will be collected and stored securely to maintain confidentiality, with only authorized personnel having access to identifiable information.

The study protocol was registered in ClinicalTrials.gov (NCT06427564). If modifications in the original protocol are required, additional amendments will be demanded by the Ethics Committee. In this scenario, the approved related information will be updated on ClinicalTrials.gov.

The authors followed the SPIRIT (Standard Protocol Items: Recommendations for Interventional Trials) guidelines for study protocol reporting (Multimedia Appendix 1) to ensure greater scientific rigor. Written informed consent will be obtained from all participants, and data collection will be performed by a trained research team.

Consent will be requested for the use of the blood sample results (complete blood count, HbA_1c_, lipid profile, glucose, and creatinine). Consenting to view the biochemical data is optional. A participant who chooses not to provide their biochemical results will still be eligible to participate and complete the recordings.

## Results

Data collection began in June 2024. As of March 25, 2025, we have recruited 1200 participants. The outcomes of the study are expected at the end of 2025. The analysis plan involves verifying and validating the parameters collected from mobile devices via the app, reference devices, and prescheduled blood tests, along with patient demographic data.

## Discussion

### Principal Findings

The project aims to report whether this user-friendly mobile app supports a high level of accuracy in monitoring SpO_2_, RR, BP, and PR, demonstrating the same reliability in detecting Hb, HbA_1c_, and total cholesterol. Enhancing algorithm performance and achieving a high level of accuracy will be crucial in assessing whether the app can be adopted to improve self-monitoring of health status. This, in turn, could enhance the screening for early abnormalities in vital signs and biochemical parameters.

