Photoplethysmography is a practical method for noncontact vital sign measurement using a red-green-blue (RGB) camera that has been recently introduced [6,9]. Photoplethysmography uses a transducer that emits infrared light from an LED into the dermis. The adjacent photodetector measures the backscattered light, which is then represented as a line tracing. The intensity of the backscattered light changes with the volume of red blood cells in the dermal capillaries [9]. Photoplethysmography captures color change signals collected from various regions of the face, correlating the estimated magnitudes of red cell aggregation influenced by blood perfusion with the reflected light intensity in each region. By comparing variations in the averaged color signals, the camera-based signal-to-noise ratio estimates are enhanced.

As reported by [10,11], photoplethysmography has shown promising results in measuring vital signs and could be a valuable tool for the early detection and screening of cardiovascular, respiratory, and metabolic conditions. These interventions could be crucial in combating noncommunicable chronic diseases (NCDs) [12]. Furthermore, literature data on the use of photoplethysmography for vital sign detection usually refer to controlled clinical settings. Larger, more diverse populations need to be included to ensure accuracy across various demographics and health conditions [10,12,13].

In this study, vital parameters will be measured using the Comestai app to confirm the accuracy of photoplethysmography methods compared to standard clinical practice devices, analyzing a large and diverse population. In addition, the app will facilitate big data collection to enhance the algorithm's performance in measuring Hb, HbA_1c_, and total cholesterol. The results will be useful to determine whether this user-friendly mobile app achieves adequate accuracy and can be adopted to enhance self-monitoring of health status and detect early health deterioration. A secondary result will be the collection of raw data that can be used to train the algorithm to detect other vitals.

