**Exclusion criteria**
Participants will be excluded if they meet any of the following conditions:Compromised circulation, injury, or physical abnormalities affecting fingers, hands, ears, forehead/skull, or other regions of interest essential for study testing.The presence of tattoos in the optical path hinders the assessment of necessary regions of interest.Severe allergies to standard adhesives, latex, or other materials used in medical sensors for measuring vital signs.Medical conditions that, in the investigator’s opinion, prevent the conduct of study assessments.Considered unfit for participation by the investigator.

Additional inclusion criteria.Prediabetes or diabetes with glycated hemoglobin (HbA_1c_) levels between 5.7% and 13%:30% of participants with HbA_1c_ 5.7%-6.4%.30% of participants with HbA_1c_ >6.4%.Hypertension with systolic measurements exceeding 130 mm Hg:40% of participants with systolic blood pressure >130 mm Hg.20% of participants with systolic blood pressure >160 mm Hg.Total cholesterol:40% of participants with levels >200 mg/dL and/or low-density lipoprotein cholesterol >130 mg/dL.Atrial fibrillation (~1% prevalence).Smokers, constituting approximately 20%-30% of the study cohort.

Procedures and evaluations.Obtain participant consent and, if agreed, additional consent for a blood sample.Review eligibility: assess eligibility as described in the inclusion and exclusion criteria.Record the participants’ medical and medication history: each medical problem encountered is classified into the sector of the body involved and for each of these, the starting date and the drugs used for treatment are indicated.Record participant demographics, including date of birth, age, smoking, and alcohol drinking habits.Record body characteristics including height, weight (BMI will be calculated as a person’s weight in kilograms divided by the square of height in meters), and skin tone using the Fitzpatrick scaleInterview the patient about his feelings in the last 2 weeks and if he has suffered from problems such as anxiety, nervousness, lack of control, loss of interest in doing things, or depression.

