### Statistical Analysis

Numerical variables will be presented as minimum and maximum values, means, SDs, medians, and quartiles. Categorical variables will be presented as absolute and relative frequencies.

The accuracy of the app measurements compared to the reference devices and standard tests will be assessed for all parameters. CIs will be calculated using the bootstrap method. Participants with abnormal adverse events (defined as 3 SDs or more above the mean) and those with invalid reference device values will be excluded from the analysis.

In order to provide a more comprehensive view of the model’s performance, the proposed approach’s effectiveness was evaluated using various quality criteria, including the mean error, SD, mean absolute error, root mean square error, and mean absolute percentage error. The correlation between measurements obtained using the app and those from reference devices and standard tests will be evaluated using the Pearson correlation coefficient. The agreement between the 2 sets of measurements (app vs reference devices/standard tests) will be represented using Bland-Altman plots. Sensitivity, specificity, positive predictive value, negative predictive value, accuracy, and likelihood ratios will be calculated to determine the ability of the new app to accurately measure vital signs.

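### The equal-reliability claim for Hb, HbA1c and total cholesterol, and the power claim for every parameter, go beyond the stated objective and the four rows of Table 2

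*Protocol article*

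**What the plan says.** **Claim for the analytes.** Principal Findings in the Discussion says the project will report whether the app is highly accurate for SpO2, respiratory rate, blood pressure and pulse rate, "demonstrating the same reliability in detecting Hb, HbA_1c_, and total cholesterol". It then links this to adoption for self-monitoring and to screening for abnormal biochemical values.

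**Objective for the analytes.** The Introduction, matching the Abstract's Objective, says "the app will facilitate big data collection to enhance the algorithm's performance in measuring Hb, HbA_1c_, and total cholesterol". For the vital signs, the same places speak of confirming accuracy against standard devices.

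**Analysis.** Statistical Analysis says: "The accuracy of the app measurements compared to the reference devices and standard tests will be assessed for all parameters". It lists mean error, SD, MAE, RMSE, MAPE, Pearson correlation, Bland-Altman plots and diagnostic measures, with bootstrap CIs.

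**Power.** Sample Size Estimation says "there will be a power exceeding 95% for all evaluated parameters". This is for 3000 participants and a two-sided 0.05 level, provided the discrepancy between methods is that of Table 2. The table has four rows: pulse rate (RMSE ≤3), respiratory rate (RMSE ≤3), systolic BP (MAE ≤15) and diastolic BP (MAE ≤10). Its title calls these values expected errors.

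**Number of blood results.** Ethics Approval makes sharing biochemical results optional. A participant who declines can still take part and complete the recordings.

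**The concern.** Two statements promise more than the described design delivers. Improving an algorithm and demonstrating that it is as reliable as an established measurement are different aims, and the article gives both for the same three analytes. The power statement covers every parameter but rests on a table with half of them.

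This bears on what the trial may conclude. If both sentences stand, a report could present Hb, HbA1c and cholesterol as validated alongside the vital signs and as backed by more than 95% power. The article fixes neither what *the same* means across beats, breaths, mm Hg, % and mg/dL nor which vital sign is the comparator. That choice could then be made after the data are seen.

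**Working it through.** **1. Coverage of the power statement.** The measurements to be evaluated are pulse (heart) rate, respiratory rate, systolic BP, diastolic BP, SpO2, Hb, HbA1c and total cholesterol: eight. Table 2 has rows for the first four. SpO2 is missing from the table although the power sentence itself refers to saturation.

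**2. Can the stated power be reproduced?** The article gives n = 3000, two-sided alpha 0.05 and power above 95%. It gives no SD of the differences and no null hypothesis, and RMSE and MAE are not mean differences, so there is no unique reproduction. Under a paired normal approximation (an assumption), the smallest detectable mean difference in SD units is

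(1.960 + 1.645)/√3000 = 3.605/54.77 = 0.0658.

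If each Table 2 limit is read as a mean difference d, power exceeds 95% whenever the SD of differences is below d/0.0658:

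| Parameter | d | SD of differences must be below |
|---|---|---|
| Pulse rate | 3 | 45.6 |
| Respiratory rate | 3 | 45.6 |
| Systolic BP | 15 | 228 |
| Diastolic BP | 10 | 152 |

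These bounds are wide next to the ranges in Table 2, so the claim is plausible for the four rows on this reading. If RMSE = 3 is taken literally (RMSE² = bias² + SD²), power depends on the bias: 5% at bias 0, 45% at 0.1 and 95.5% at 0.2.

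For SpO2, Hb, HbA1c and total cholesterol there is no d, so the formula cannot be applied.

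**3. Sample for the analytes.** The number consenting to share blood results is not given. If the share is f (an assumption), the detectable standardised difference becomes 0.0658/√f:
- f = 1 (n = 3000): 0.066
- f = 0.5 (n = 1500): 3.605/38.73 = 0.093
- f = 0.25 (n = 750): 3.605/27.39 = 0.132

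**4. Does Table 2 supply a common standard? (illustration only)** Assume unbiased normal error, so that MAE = 0.798 × RMSE, and express each value as relative MAE. The resting values are also assumed.

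| | Pulse | Resp. rate | Systolic | Diastolic | Ratio to pulse |
|---|---|---|---|---|---|
| Range mid-points (115, 19, 130, 85) | 2.1% | 12.6% | 11.5% | 11.8% | 5.5–6.1 |
| Resting values (72, 16, 130, 80) | 3.3% | 15.0% | 11.5% | 12.5% | 3.5–4.5 |

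Scaling to range width on the same metric takes the ratio up to 8.2. Scaling to the lower end of each range without conversion takes it down to 3.1. The ratio is therefore about 3 to 8. Pulse rate drives it: the other three values differ by only about 1.1-fold at mid-points and 1.3-fold at resting values.

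Carried to HbA1c 6.05%, the pulse-like relative error is an MAE of 0.13–0.20 points, and the BP- or respiratory-like error is 0.70–0.91 points. The prediabetes recruitment band of 5.7–6.4% in Textbox 2 is 0.7 points wide. This shows why an undefined comparator matters. It does not predict how the app will perform.

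**The case against.** **It is one loose sentence in a Discussion.** It speaks of aiming to report whether the app is accurate, and the article sets no equivalence hypothesis, margin or between-parameter test. This stands: a reader might infer a formal equivalence aim lacking its test, and the text does not support that. It does not remove the conflict with the Introduction, because the sentence still says what is to be demonstrated and leads on to adoption and screening.

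**Acceptance limits may exist elsewhere.** The full protocol and the analysis plan are not shown and could hold limits for the analytes. This also stands, so their absence here is not the finding. Such limits would not correct an objective stated in two ways, or a power sentence wider than its own table.

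**Table 2 holds no pass marks.** A reader might infer that the table sets pass marks several-fold apart, so that the claim could never be decided. The table gives expected errors used as power assumptions, nothing says that they carry over to blood tests, and the ratio depends on a scaling the plan does not state. That reading is not supported.

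**The power sentence may mean only the vital signs.** It opens with pressure, saturation and heart rate. On that reading SpO2 still lacks a row, while respiratory rate has a row but is not named. Elsewhere the article counts comparisons with standard tests among its parameters.

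**Poor accuracy would be visible, and no medical decision uses the data.** Both are true: errors are to be reported with CIs, and Data Collection and Management rules out clinical use. This limits the harm to participants but not the risk of an over-strong published conclusion.

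**Conclusion.** The point holds as a mismatch within the article. For Hb, HbA1c and total cholesterol, the equal-reliability statement goes beyond the algorithm-development objective, and no described analysis compares reliability between parameters. The power statement is supportable for at most four of eight measurements, and for those only if the Table 2 values are read as mean differences in a paired test. No power follows for the other four. For the three blood analytes the sample may also be smaller than 3000; by how much is unknown.

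The conclusion on coverage needs no distributional assumption. The relative-error and HbA1c figures assume unbiased normal error and a chosen scaling, and the conclusion does not depend on them. Whether adequate accuracy for the analytes can be decided at all is not settled here, since the full protocol and analysis plan are not shown.

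**What to change.** 1. In Sample Size Estimation, limit the power statement to the four parameters in Table 2.
2. In Principal Findings, replace the equal-reliability phrase. State that the accuracy of Hb, HbA1c and total cholesterol will be estimated with bootstrap CIs, in line with the Abstract and Introduction. Add that no conclusion of equal or adequate reliability will be drawn for an analyte unless a numerical limit in its own unit is fixed before the analysis and the upper confidence bound of the error measure lies below it.

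If the full protocol or analysis plan already holds such limits, a cross-reference is enough for the condition in item 2.

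**Cost.** The change is to wording only, with no extra participants, visits or tests, and the bootstrap CIs are already planned. The price is a weaker headline claim for the blood parameters.

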### Strengths and Limitations

Today’s health care industry embraces technological innovations to provide better personalized health care services to the public [17]. Mobile-based solutions and apps are one such revolutionary and trending innovation that facilitates enhanced patient care management and efficient diagnosis. They are increasingly reliant on wireless technologies as they evolve [17]. Applications of mHealth typically include the use of mobile devices in the collection of health and clinical data, the provision of health information to practitioners, researchers, and patients, the real-time monitoring of patients; vital signs, and the direct delivery of care (via mobile telemedicine).

In an mHealth context, the advancement of noncontact methods to monitor human vital signs holds substantial promise for enhancing patient care across various environments [6].

A recently proposed RGB camera–based method for noncontact vital sign measurement using photoplethysmography has been identified as an interesting tool for recording vital signs. Photoplethysmography is also used by the Comestai app to assess various vital functions, including SpO_2_, RR, BP, and PR [10]. Initial research into photoplethysmography shows promising outcomes; however, scientific evidence regarding the accuracy and benefits of digital health apps that measure vital signs remains limited and somewhat controversial. Many photoplethysmography studies are still susceptible to errors [18-20], with the majority involving only small sample sizes.

In our protocol, we will recruit a large population (3000 participants) to ensure accuracy across various demographics and health conditions, including also pathological conditions. The use of a large population will also help reduce errors in the results, improving the reliability of the tool. Thorough analysis and classification of these signals are essential for the development of affordable and user-friendly PPG-based tools across a wide range of applications [10].

While there is an increasing number of articles and research on SpO_2_, RR, BP, and PR monitoring using PPG, a limited number of available publications on advancements related to biochemical parameter estimation are reported [10]. Comestai offers the possibility to monitor Hb, HbA_1c,_ and cholesterol concurrently with other parameters, thereby broadening its application possibilities in health care services.

Although the protocol included participants with diseases such as hypertension, prediabetes and diabetes, dyslipidemia, and atrial fibrillation to assess the tool’s accuracy even in the presence of pathological values, conducting the study in a controlled setting can be considered a limitation. Its application in real-life scenarios may present challenges that were not accounted for.

### Future Research

As suggested by the World Health Organization (WHO), it is important to disseminate medical procedures and health programs based on mHealth [21]. Mobile apps have become increasingly popular among professionals and individuals involved in the health care sector, with a variety of mHealth apps developed to improve health care facilities for all kinds of patients [22,23]

Specifically, mobile apps can play a vital role in screening, leading to the early detection of vital sign alterations, which is useful for alerting individuals and their caregivers to access medical care services and design and implement treatment plans. Screening is considered a crucial player in addressing chronic noncommunicable diseases (NCDs), which are responsible for nearly 70% of all deaths worldwide [12,24,25].

According to the WHO [12], NCDs cause 41 million deaths each year. This burden is expected to grow over the next decade, with NCD deaths projected to reach 52 million by 2030. Cardiovascular diseases are the leading cause of NCD deaths, accounting for 17.9 million fatalities annually. They are followed by chronic respiratory diseases (4.1 million) and diabetes (2.0 million, including kidney disease deaths linked to diabetes). Early detection and screening are vital strategies in combating NCDs. Disease screening detects diseases early, often before symptoms appear, through tests, examinations, or other rapid procedures [26]. This early detection enables effective prevention or treatment of identified diseases through timely medical intervention for those at risk [27].

Despite screening being recognized as the gateway to care, routine NCD screening at community and health facilities remains challenging due to limited capacity within health systems. A screening tool must be simple, valid, reliable, quick to administer, cost-effective, and user-friendly [23]. According to reports, photoplethysmography wearables have significant potential for estimating the risk of cardiovascular diseases [28], predicting suspected sleep apnea [29,30], and helping in the clinical diagnosis of hypertension [31] and diabetes. This potential can be harnessed through app solutions.

Recent reviews have assessed the role of apps in aiding self-management and transition among chronically ill young people, enhancing the lifestyles of chronic patients, and improving lifestyle in NCDs [32]. As reported by Moses et al [27], regardless of a country’s economic status, there has been a rise in mobile cellular subscriptions per hundred people in developing nations, mobile app solutions may provide equitable health care solutions without barriers.

